## Abstract

**Background:**

There is an urgent need to develop additional treatment strategies for patients with treatment-resistant depression (TRD). The rapid but short-lived antidepressant effects of intravenous (IV) ketamine as a racemic mixture have been shown repeatedly in this population, but there is still a paucity of data on the efficacy and safety of (a) different routes of administration, and (b) ketamine’s enantiomers esketamine and arketamine. Given practical advantages of oral over IV administration and pharmacodynamic arguments for better antidepressant efficacy of esketamine over arketamine, we designed a study to investigate repeated administration of oral esketamine in patients with TRD.

**Methods:**

This study features a triple-blind randomized placebo-controlled trial (RCT) comparing daily oral esketamine versus placebo as add-on to regular antidepressant medications for a period of 6 weeks, succeeded by a follow-up of 4 weeks. The methods support examination of the efficacy, safety, tolerability, mechanisms of action, and economic impact of oral esketamine in patients with TRD.

**Discussion:**

This is the first RCT investigating repeated oral esketamine administration in patients with TRD. If shown to be effective and tolerated, oral esketamine administration poses important advantages over IV administration.

**Trial registration:**

Dutch Trial Register, NTR6161. Registered 21 October 2016.

## Background

Major depressive disorder (MDD) is one of the most impactful medical conditions worldwide in terms of individual suffering, loss of productivity, and health care costs [1, 2]. Unfortunately, current treatments for depression fail to achieve remission in approximately 30% of patients [3]. This is known as treatment-resistant depression (TRD).

TRD contributes disproportionately to the disease burden of MDD. This burden exponentially increases the longer TRD persists, with increasing risk of impaired functional and social functioning [4], vast losses in quality of life for both patients and people close to them [4, 5], and increasing risk of somatic morbidity [6, 7]. Moreover, TRD is associated with an impressive financial burden to society, due to patients’ more extensive and costly use of medical services, as well as to their loss of productivity [4, 5, 8]. Hence, there is an urgent need to develop more efficacious therapeutic strategies for MDD generally, and for TRD specifically.

It has been two decades since a single intravenous (IV) administration of the anaesthetic agent ketamine was first reported to have antidepressant effects in patients with MDD [9]. Since then, accumulating data have confirmed ketamine’s antidepressant effects [10, 11]. Two features of these data are most striking. Firstly, response can become manifest within hours after administration. Secondly, this response takes place even in patients with TRD.

In most patients, the therapeutic effects of a single IV administration of ketamine last about 1 week [11, 12]. These effects can be extended with repeated IV administration [13–15]. However, this procedure is invasive, costly, and often brings about acute psychiatric (e.g., dissociation, anxiety, agitation) and somatic (e.g., headache, dizziness, cardiovascular) side effects [16]. These disadvantages present major obstacles to clinical applicability, especially in community settings.

To date, several uncontrolled studies (reviewed by [name] et al. [17] and Rosenblat et al. [18]) and three small controlled studies [19–21] have reported on the antidepressant properties of oral ketamine. They suggest that oral ketamine may also be effective in patients with TRD, and that side effects are overall more acceptable compared to IV administration. Besides, data from chronic pain management indicate that oral ketamine can often be safely used for longer periods of time, including at home [17]. Thus, oral ketamine may be a suitable alternative for IV ketamine in the treatment of TRD. However, the literature on oral ketamine is scarce, and the bioavailability of oral ketamine has been little studied. There remains a need to conduct larger controlled studies, and to examine the pharmacokinetics and pharmacodynamics of oral ketamine [22].

In most TRD studies conducted to date, ketamine has been administered as a racemic mixture comprised of the R-(−) enantiomer of ketamine (arketamine) and the S-(+) enantiomer (esketamine). In the brain, ketamine modulates glutamate transmission by acting as an N-methyl-D-aspartic acid (NMDA) receptor antagonist. The NMDA receptor binding affinity of esketamine is three to four times higher than that of arketamine [23, 24]. As the majority of ketamine’s antidepressant properties are believed to stem from its impact on glutamate neurotransmission, theoretically esketamine might yield the best therapeutic effect. Indeed, rapid and robust antidepressant effects of esketamine have been observed in patients with TRD [25–27]. Besides, compared to racemic ketamine and arketamine, esketamine is believed to have fewer side effects [26, 28, 29]. To date there have been no controlled oral esketamine studies.

Ketamine also has other effects that may be linked to its antidepressant properties. It is used for the treatment of chronic pain [17] and treatment-resistant anxiety disorders [30], conditions that are often comorbid with MDD [31, 32]. Besides, ketamine could play a role in smoking cessation, as the pharmacodynamic effects of nicotine may involve NMDA receptors [33].

In summary, given (1) the advantages of oral over IV administration, and (2) pharmacodynamic arguments for a better antidepressant efficacy of esketamine over racemic ketamine and arketamine, oral esketamine is a promising addition to our currently available treatment armamentarium for depression. To investigate repeated administration of oral esketamine in patients with TRD, we designed a triple-blind randomized controlled trial (RCT).

The primary aim of this RCT is to examine the antidepressant properties of oral esketamine in patients with TRD, as determined using clinician rating scales. Secondary aims involve the effects of oral esketamine on self-reported severity of depression, depressive symptom dimensions, hedonic capacity, suicidal ideation, cognitive functioning, quality of life, safety, tolerability, and its effects in specific subgroups of patients. Apart from these aims, we will address additional relevant questions regarding (1) therapeutic effects of oral esketamine on pain, anxiety and nicotine addiction, (2) its bioavailability and mechanism of action, and (3) its economic impact.

## Methods

### Study design

This study features a triple-blind RCT with two parallel arms, as add-on to regular antidepressant medication: an esketamine (intervention) group and a placebo (control) group. The study has a total duration of 10 weeks: 6 weeks of study medication and 4 weeks of follow-up. All patients who complete the trial are subsequently offered an off-label esketamine treatment extension. This extension will be described in more detail elsewhere.

### Study management

This study is approved by the Medical Ethics Review Committee of the University Medical Center Groningen (UMCG) in the Netherlands (file number M16.198879) and registered at the Dutch Trial Register (trial number NTR6161). The independent Clinical Research Office (CRO) of the UMCG and an independent Data Safety and Monitoring Board (DSMB) oversee the conduct of the study. The CRO executes an audit of the trial system twice a year. The DSMB meets every 6 months to discuss study progress and patient safety and provide feedback to the investigators.

The study is conducted at three centers in the Netherlands: University Center of Psychiatry in Groningen, Pro Persona Depression Expertise Center in Nijmegen, and Parnassia Psychiatric Institute in The Hague.

### Study treatment

Patients randomized to the intervention arm take capsules containing oral esketamine three times a day during 42 consecutive days. During the first 3 days, dosages are gradually increased from 10 mg at administration 1 (day 1) to 30 mg at administration 9 (day 3). During the last 3 days, dosages are gradually decreased from 30 mg at administration 118 (day 40) to 10 mg at administration 126 (day 42). Patients randomized to the control arm take placebo capsules containing microcrystalline cellulose and magnesium stearate. Treatment compliance is assessed during every visit.

### Sample

#### Recruitment

Psychiatry departments and patient and family associations throughout the Netherlands are involved in recruitment, and advertisement takes place by various media. Prior to screening, potential participants receive an oral and written explanation of study procedures, potential benefits, and potential risks. They are informed that participation is voluntary and that they are free to withdraw at any time for any reason. Before enrolment, written informed consent is obtained from each patient.

#### Eligibility

Patients are selected for study enrolment based on the inclusion and exclusion criteria listed in Table 1. During the study, investigators can decide to withdraw a participant for urgent medical reasons, or if the situation of a participant changes such that he or she is no longer eligible to participate.

**Table 1 Tab1:** Inclusion and exclusion criteria

Subject eligibility	
Inclusion criteria	1. Age 18 to 80 years; 2. Current major depressive episode according to the DSM-5, ascertained by the MINI; 3. Depression at least moderately severe, defined by a score > 18 on the HDRS_17_; 4. TRD, defined as insufficient lifetime response to 3 or more different classes of antidepressant drugs, given for at least 4 weeks and in an adequate dose; 5. Stable dose of current antidepressant drug for at least 4 weeks prior to study initiation; 6. Good understanding of spoken and written Dutch.
Exclusion criteria	1. Meet DSM-5 criteria for current major depressive episode with psychotic features, bipolar disorder, past or current psychotic disorder, past or current moderate or severe substance dependence, or personality disorder as a primary diagnosis; 2. Recent (within the last 4 weeks) or current use of non-prescribed psychoactive compounds; 3. Recent (within the last 4 weeks) or current use of benzodiazepines in excess of 2 mg lorazepam or equivalent per day; 4. Current electroshock therapy; 5. Active suicidal intent, defined by a score > 2 on item 3 of the HDRS_17_; 6. Pregnancy or lactation; 7. A relevant somatic disorder, ascertained by physical examination, electrocardiogram, and blood tests; 8. Use of medication that ketamine interacts with on a major level according to the Drug Interactions Checker [34], including monoamine oxidase inhibitors.

*DSM-5* 5th edition of the Diagnostic and Statistical Manual of Mental Disorders [35], *HDRS*_17_ 17-item Hamilton Depression Rating Scale [36, 37], *MINI* Mini International Neuropsychiatry Interview [38], *TRD* Treatment-resistant depression

#### Statistical power

At the time of sample size calculation, one open-label study had shown antidepressant effects of oral racemic ketamine in 57% of patients [39]. Previously, another open-label study had shown antidepressant effects of oral esketamine in 50% of patients [40]. This indicates a response rate of oral (es)ketamine of 50–57%. As the lack of a control group in these studies might have inflated response rates, in the present trial a response rate of 40% was estimated for the intervention group. For the control group, a response rate of 15% was estimated. This was based on previous studies showing a placebo response in 14.4% of TRD patients [41].

To detect a significant difference in response rate between groups, with the two-sided significance level set at 95% (α = 0.05) and a power of 0.8, 57 participants per group should complete the trial. Assuming a 10% drop-out rate, 64 participants will be included in both groups, leading to a total of 128 participants.

### Randomization and blinding

Participants are randomly allocated in a 1:1 manner to either treatment group. Randomization is conducted through ALEA Clinical web application. Blinding takes place at the level of participants, clinicians, and study staff. Placebo capsules are matched to esketamine capsules in shape, smell, and colour. All capsules are sealed in identical blisters. Blisters are labelled as trial medication, and given a trial number by the manufacturer ACE Pharmaceuticals. A list with trial medication numbers and the corresponding allocated treatment is stored at the Department of Clinical Pharmacy and Pharmacology of the UMCG. None of the study team members have access to the list until the trial is finished, or unless something unexpected happens that warrants breaking the blind. The success of blinding is tested by asking participants and data collectors at the end of the intervention period which group they thought participants were in, and by comparing these data with the allocation data after unblinding.

### Tests and measures

#### Testing procedure

All participants are measured before (at baseline), during (after 1, 2 and 4 weeks), and at the end (after 6 weeks) of treatment. Additionally, to determine how long therapeutic effects can be retained, follow-up assessments are planned after 1 (week 7), 2 (week 8) and 4 (week 10) weeks. All data are entered electronically. Original study forms are stored in a secure and accessible place and manner. Figure 1 represents the research procedure schematically.

**Fig. 1 Fig1:**
[figure not shown]
Trial flowchart. Schematic overview of the study design. T: Number illustrates number of weeks after baseline

#### Primary outcomes

In line with the primary aim of the study, antidepressant efficacy is measured by 1) response, defined as ≥50% decrease in total 17-item Hamilton Depression Rating Scale (HDRS_17_) score between pre-treatment and end-of-treatment; 2) partial response, defined as 25–49% decrease in total HDRS_17_ score between pre-treatment and end-of-treatment; 3) change in depression symptom severity, expressed as a change in total HDRS_17_ score between pre-treatment and end-of-treatment. The HDRS_17_ is a 17-item clinician-rated semi-structured interview [36, 37], that is used to assess the severity of depressive symptoms. The HDRS_17_ is completed only by trained clinicians and researchers. Inter-rater reliability is determined twice a year: an intraclass correlation coefficient of > 0.50 (at least moderate agreement) is pursued [42].

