### Statistical analysis plan

The efficacy and safety of esketamine will be tested by the use of intention-to-treat and per-protocol linear and logistic mixed models. The effects on biomarker patterns will be tested using Receiver Operating Characteristics (ROC) analyses in combination with phenotype randomization. Pharmacokinetic models will be built by using population pharmacokinetic modelling software (MWPharm) using Iterative-2-stage Bayesian techniques, and will include the absorption (esketamine) or formation (esnorketamine) constant, bioavailability, volume of distribution (relative to bioavailability), and total body clearance (relative to bioavailability). Next, these models will be used to make an estimation of exposure. These data will be analysed using descriptive statistics. The relationship between exposure variables, efficacy and safety will be explored by using regression models and box-and-whisker plots.

EQ-5D-5 L data will be converted into Quality Adjusted Life Years (QALYs) using the Dutch tariffs [64]. Healthcare resource use, loss of productivity, and informal care will be recalculated into societal costs according to the Dutch guidelines for economic evaluation in healthcare [65]. Cost-effectiveness and cost-utility will be reported as incremental costs per point gained on the HDRS_17_ and per QALY gained, respectively. Uncertainty surrounding the outcomes will be assessed by bootstrap analyses and cost-effectiveness acceptability curves.

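### Three unranked primary outcomes, but alpha, power and sample size are set for response alone

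*Protocol article*

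**What the plan says.** Three sections of the protocol article bear on this.

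- **Primary outcomes.** The first outcome is response: "antidepressant efficacy is measured by 1) response, defined as ≥50% decrease in total 17-item Hamilton Depression Rating Scale (HDRS_17_) score". The second is "2) partial response, defined as 25–49% decrease in total" HDRS17 score. The third is "change in depression symptom severity, expressed as a change in total HDRS_17_ score between pre-treatment and end-of-treatment". The three are numbered, but nothing says that the numbers are a testing order, or whether one or all must succeed.
- **Statistical power.** The calculation is for one comparison: "To detect a significant difference in response rate between groups, with the two-sided significance level set at 95% (α = 0.05", power 0.8. It assumes response in 40% on esketamine and 15% on placebo. The result is 57 completers per group, raised to 64 per group (128 in total) for 10% drop-out.
- **Statistical analysis plan.** "The efficacy and safety of esketamine will be tested by the use of intention-to-treat and per-protocol linear and logistic mixed models". The sentence does not say which set leads, or which model answers the primary question.

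**The concern.** The choice of primary outcome belongs to the protocol, and this article makes that choice: three outcomes, all primary. The error rate and power are stated for only one of them. A reader cannot tell which result is the trial's answer if response, partial response and change disagree, and the choice could then be made after the data are seen.

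Two decision rules are possible on the present wording. Either any of the three may support efficacy, in which case 5% is not the error rate of the conclusion, or all three must succeed, in which case 80% is not its power. What is at stake is whether the figures under Statistical power describe the trial's conclusion or only one of its tests.

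**Working it through.** **1. The plan's own figure.** Inputs from Statistical power: p1 = 0.40, p2 = 0.15, mean 0.275, z = 1.960 (two-sided 0.05) and 0.842 (power 0.8).

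n = [1.960·√(2·0.275·0.725) + 0.842·√(0.40·0.60 + 0.15·0.85)]² / 0.25² = (1.238 + 0.510)² / 0.0625 = 48.9.

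With continuity correction: (48.9/4)·[1 + √(1 + 4/(48.9·0.25))]² = 56.6, so 57. Then 57/0.9 = 63.3, so 64 per group and 128 in total. The published figures reproduce exactly, for the single test of response.

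**2. If any one of three may carry the claim.** Three independent tests at 0.05 would give 1 − 0.95³ = 14.3%. The three outcomes come from the same scores and are correlated, so this was simulated under no treatment effect, with 20,000 trials per setting and 57 or 64 patients per arm. Baseline HDRS17 was about 22.5 (SD 4) and at least 19, since eligibility requires a score above 18. Percentage decrease was normal, with SDs between 22 and 36 points, placed so that about 15–16% respond. Response and partial response were compared by a pooled z-test and change by a t-test, each at two-sided 0.05, as simple stand-ins for the planned mixed models. The baseline values, the SDs and the normal shape are assumptions; the article gives none of them.

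| Counted as success (intention-to-treat) | Two-sided | Favouring esketamine |
|---|---|---|
| One test | 5% | 2.5% |
| Response or change | 8–9% | about 4% |
| Any of the three | 12–13% | 6–7% |

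The results varied little across the distributions tried.

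**3. If all three must succeed.** Partial response excludes responders, so an effective treatment moves patients into the 25–49% band from below and out of it from above. Let percentage decrease be normal with SD s, and set each arm's mean so that 15% or 40% exceed 50%. For s = 29, the placebo mean is 50 − 1.036·29 = 19.9 and the esketamine mean is 50 − 0.253·29 = 42.7. The share above 25% is 43.1% on placebo and 72.9% on esketamine. Subtracting responders leaves 28% and 33% in the band.

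| Assumed SD | Partial response, placebo | Partial response, esketamine | Power for partial response, 57 per arm (two-sided) |
|---|---|---|---|
| 22 | 39% | 41% | 6% |
| 29 | 28% | 33% | 9% |
| 36 | 22% | 27% | 10% |

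Simulated at 57 per arm, the chance that all three are significant in favour of esketamine is about 2% to 7%, against the 80% stated.

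**4. Cost of keeping three primaries with a Bonferroni split.** At alpha 0.05/3, the continuity-corrected formula in step 1 gives 74 completers per arm. Then 74/0.9 = 82.2, so 83 randomised per arm and 166 in total.

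**The case against.** The strongest reply is that an article condenses a fuller plan. Test order, multiplicity handling and the leading analysis set are commonly left to the SAP, which is not shown and may settle them. That is right, and their absence is not the finding. What stands is a conflict inside the article: three outcomes are declared primary, and the error rate and power are given for one.

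Response is also numbered first and is the only outcome with an alpha, a power and a sample size. This suggests that it was meant to lead, but a suggestion is not a rule, and the text calls all three primary.

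A reader might infer more than the documents support:

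- **Six tests and an error rate of 16–19%.** Adding per-protocol tests gives this range if 10–30% of patients are excluded at random. But the article says only that efficacy "will be tested by the use of intention-to-treat and per-protocol linear and logistic mixed models". It does not give the two sets equal standing or say that a per-protocol result may carry the claim, and the exclusion rates are assumed. The point is therefore made on intention-to-treat alone.
- **A 12–13% chance of falsely claiming that esketamine works.** That figure counts differences in both directions. A false result in favour of esketamine has a chance of about 6–7%, to be compared with 2.5%.
- **Partial response as an efficacy win.** A difference in the 25–49% band does not by itself show benefit, since an effective drug can also empty it. Leaving it out gives the 8–9% figure.

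**Conclusion.** The point holds as a mismatch between Primary outcomes and Statistical power. The sample size is correct for the test it names. It does not describe a conclusion drawn from three primary outcomes under either simple rule. Letting any outcome suffice raises the two-sided false-positive chance from 5% to about 12–13% (about 8–9% for response and change only). Requiring all three brings power from 80% down to a few per cent.

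The first figure assumes unadjusted tests at 0.05 and that one success is enough, neither of which the article states. If all three had to succeed, there would be no inflation, but the loss of power applies instead. Both calculations rest on assumed HDRS17 distributions, with ranges shown. A fuller SAP may already name one leading test. If so, the article's list of primary outcomes should be brought into line with it.

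**What to change.** Recruitment was still under way when the article was written (Discussion), so the change can be made in protocol and SAP wording before unblinding:

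1. Name response at week 6 in the intention-to-treat set, the outcome used for sizing, as the single confirmatory primary test at two-sided 5%.
2. Test change in HDRS17 at week 6 next, at two-sided 5%, only if response is significant.
3. Move the 25–49% band to secondary or descriptive status. Alternatively, replace it with a cumulative decrease of at least 25%, and state that this redefines the outcome.
4. Label the per-protocol analysis as supportive.

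The total stays at 128 and power for response is unchanged. The cost is that lower-ranked outcomes lose confirmatory status if response fails. Keeping all three as primaries under Bonferroni would instead take about 166 randomised to hold 80% power for response, and would still leave the 25–49% band uninformative.

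### Partial response, a primary outcome, is a closed 25–49% band that excludes full responders; if it is analysed alone as yes/no, its direction and size do not show efficacy

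*Protocol article*

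**What the plan says.** The section on primary outcomes introduces three numbered measures with the words "In line with the primary aim of the study, antidepressant efficacy is measured by 1) response". All compare HDRS17 before treatment with HDRS17 at its end.

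- The first is full response, a fall of at least half: "response, defined as ≥50% decrease in total 17-item Hamilton Depression Rating Scale".
- The second, the one at issue here, is worded as "partial response, defined as 25–49% decrease in total HDRS_17_ score between pre-treatment and end-of-treatment".
- The third keeps the same scale continuous and is worded as "change in depression symptom severity, expressed as a change in total HDRS_17_ score between pre-treatment and end-of-treatment".

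The first two are adjacent and do not overlap: a patient with a decrease of 50% or more belongs to the first and not to the second. The section does not pool the band with response, does not make it one level of an ordered outcome and does not call it descriptive.

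The analysis section says that efficacy and safety "will be tested by the use of intention-to-treat and per-protocol linear and logistic mixed models". It does not assign a model to each outcome, and it names no ordinal model.

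The section on statistical power sizes the trial on response alone: "in the present trial a response rate of 40% was estimated for the intervention group", against an assumed 15% on placebo.

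**The concern.** A primary efficacy outcome should move in one direction as patients do better. A middle band does not. Treatment lifts some patients from below 25% into the band and lifts others out of it to 50% or more. The net change depends on where the placebo distribution lies, not only on how well the drug works.

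If the outcome is coded yes/no, full responders share the no category with patients who did not improve or who worsened. A working drug could then show no difference on a primary outcome, or fewer partial responders than placebo. A drug that only turned would-be full responders into partial responders would look beneficial. At stake is whether one of the three primary results can be read by itself as evidence for or against efficacy.

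**Working it through.** **Inputs from the protocol article.** Response 15% (placebo) and 40% (esketamine), two-sided α = 0.05, power 0.80, 57 completers per group, 10% drop-out, 64 per group enrolled.

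**The plan's own figure.** For two proportions,

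n = [z(0.975)·√(2·p̄·(1−p̄)) + z(0.80)·√(p₁(1−p₁) + p₂(1−p₂))]² / (p₁−p₂)²,

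with p₁ = 0.40, p₂ = 0.15, p̄ = 0.275. This gives 48.9, so 49 per group. The continuity correction, n/4·[1 + √(1 + 4/(n·|p₁−p₂|))]², gives 56.6, so 57. Then 57/0.90 = 63.3, so 64 per group and 128 in all. The plan's figure is reproduced, and it concerns response only.

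**Illustration without a distribution.** Assume that 30% of placebo patients fall in the band, and that esketamine moves 25% of all patients from partial to full response and changes nothing else. Response rises from 15% to 40%, exactly as planned. The band falls from 30% to 5%. This shows what is possible, not what is likely.

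**Expected size under a model.** Assume that the percentage decrease in HDRS17 is normal with the same SD in both arms. The article gives neither the SD nor the placebo mean m, so m is varied. The planned response rates fix the rest:

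- SD = (50 − m)/z(0.85), with z(0.85) = 1.036
- esketamine mean = 50 + z(0.40)·SD, with z(0.40) = −0.253
- band = P(25 ≤ X < 50); cumulative outcome = P(X ≥ 25)

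Example, m = 20: SD = 30/1.036 = 28.9; esketamine mean = 50 − 0.253 × 28.9 = 42.7. P(X ≥ 25) is 43.1% and 72.9%. Subtracting 15% and 40% leaves bands of 28.1% and 32.9%.

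Power is by exact enumeration of the two-sided chi-square test without continuity correction, 57 per arm.

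| Placebo mean | SD | Band, placebo → esketamine | Difference (points) | Power | ≥25%, placebo → esketamine | Power |
|---|---|---|---|---|---|---|
| 0 | 48.2 | 15.2 → 20.4 | +5.2 | 12% | 30.2 → 60.4 | 91% |
| 10 | 38.6 | 19.9 → 25.3 | +5.5 | 11% | 34.9 → 65.3 | 91% |
| 20 | 28.9 | 28.1 → 32.9 | +4.8 | 9% | 43.1 → 72.9 | 90% |
| 25 | 24.1 | 35.0 → 38.3 | +3.3 | 7% | 50.0 → 78.3 | 90% |
| 30 | 19.3 | 45.2 → 45.1 | −0.1 | 5% | 60.2 → 85.1 | 87% |
| 35 | 14.5 | 60.5 → 53.0 | −7.5 | 12% | 75.5 → 93.0 | 75% |

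In the last row, the 12% is the chance of a significant result in either direction, and the expected difference is in the wrong one. Response itself has about 87% power by the same test.

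**Not monotone in benefit.** With SD 25 and the mean shifted to give response rates of 15%, 30%, 40%, 50% and 70%, the band is 33.5%, 38.3%, 37.2%, 34.1% and 23.6%. It rises and then falls as the drug gets better.

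**A stronger effect than planned.** With 60% response against 15%, the band changes by +2.8, +2.4, +1.7, +0.6, −1.3, −4.9 and −11.3 points at placebo means of 0, 5, 10, 15, 20, 25 and 30. The sign depends on the placebo mean.

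**The case against.** The strongest reply is that the article nowhere says the band is tested alone as yes/no. The analysis section covers all efficacy and safety outcomes in one sentence. Full responders could be coded as no, set aside, or kept as the top level of an ordinal or multinomial model. Two adjacent, non-overlapping categories on one scale would fit a graded none/partial/full classification, and coding is often left to a full protocol or SAP, neither of which is shown. This stands in part: the yes/no coding is inferred. But the article does not state the graded reading either, and it does fix the band and its place among the primary measures.

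A reader might infer that the band is expected to point to harm when the drug works as planned. The figures do not support that. For placebo means of 0–25% the band rises slightly, and at 30% it is flat. A clear fall at the planned effect needs a placebo mean of about 35%. At 60% response, which is not planned, it still rises slightly for placebo means of 0–15%.

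A reader might also infer that the band uses up part of the significance level. The article states no alpha split or hierarchy, so this cannot be said.

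Finally, response and total HDRS17 change are sound and will be reported alongside, so a fall in the band with a rise in response can be understood. That is true, and it limits the harm. It does not make the band informative by itself.

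**Conclusion.** The point holds conditionally. The definition and primary status of the 25–49% band are stated; the yes/no analysis is the natural reading but is not stated. On that reading the outcome is not monotone in benefit. At the planned effect it would most likely show little: −0.1 to +5.5 points and 5–12% power over placebo means of 0–30%, with a fall of 7.5 points at 35%.

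These sizes rest on an equal-SD normal model, on placebo means that the article does not give, and on a chi-square test in 57 completers per arm rather than the planned mixed models. That the band is not monotone does not depend on those choices.

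The other two primary outcomes and the sample size are unaffected, and the main efficacy conclusion does not hang on the band. It should be fixed before unblinding, but it does not threaten the trial.

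**What to change.** Choose one of the following and state it before unblinding:

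- Define the second primary outcome as a decrease in HDRS17 of at least 25%, full responders included. Under the model above its power is 87–91% for placebo means of 0–30% and 75% at 35%. It never counts a full responder as a failure. It would be flat if the drug only moved patients from partial to full response (45% in both arms in the illustration), but response would capture that shift.
- Analyse decreases of <25%, 25 to <50% and ≥50% as ordered categories in one ordinal (for example proportional-odds) model.

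In either case, report the 25–49% band descriptively only. If a graded analysis was always intended, a sentence saying so is enough.

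The cost is one outcome definition or one model statement in the protocol or SAP. It uses the HDRS17 scores already collected and needs no added visits or patients. The article reports that recruitment was still open.
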